### Comparator groups

In order to evaluate the influence of sorafenib on HCC treatment patterns in China, clinical outcomes will be compared across 2 periods within the overall study duration: (1) the period when sorafenib was unavailable (2005 to 2007) and (2) the period when sorafenib was available for use (2008 to 2011). These 2 periods will be differentiated by the first record of sorafenib use at each site. Patients treated during the period when sorafenib was not available will act as historic controls and will be statistically matched within the pool of patient data by age, sex, Child-Pugh status, and HCC stage to patients treated with sorafenib between 2008 and 2011. Patients treated with non-sorafenib therapies during the period when sorafenib was available will act as concurrent controls and will be used to evaluate characteristics of HCC patients treated with sorafenib versus other therapies. In this study, "sorafenib treatment" is defined as the use of either sorafenib alone or concomitant use of sorafenib and other pharmacologic agents or interventions within 21 days of each other.

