### Sample size

Sample size requirements for the Chinese regional sites are approximately 200 patients per site per year between 2008 and 2010 (plus approximately 192 per site for the first 6 months of 2011) to capture current treatment and clinical outcomes in HCC, and 100 patients per site between 2005 and 2007 for historic controls. Pooling of data across all sites in China will be employed to describe disease and treatment characteristics across the country.

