### Data analysis

To evaluate therapeutic approaches to HCC in China, the number and percentage of patients using each treatment (plus any new treatments that are approved and used within the study period) will be determined for each study year, in total and stratified by disease stage and site. Treatment patterns will also be assessed by disease stage for each study year. Patient characteristics will be stratified by disease stage and by site for each study year.

To assess therapeutic outcomes, age- and gender-adjusted rates will be calculated for each study end point. Cox proportional hazard models will be used for the time-to-event end points (overall survival and disease progression) to determine hazard ratios for each treatment approach, and Kaplan-Meier curves will be generated. Logistic regression models will be used for categorical end points (treatment-limiting adverse events and treatment failure). Covariates for the models will include disease stage, gender, age, duration of disease, etiology of disease, liver status, tumor size/spread, surgical intervention/number of interventions, and number of comorbidities; analyses will be conducted at the site and country level. The same analysis plan will be adopted for the evaluation of survival and other clinical end points with sorafenib versus other therapies, except that "treatment" will be included as a covariate. Further analyses will be conducted to evaluate clinical characteristics and demographics of patients treated with sorafenib versus other treatments for HCC. In addition, data collected will be used to analyze additional aspects related to HCC epidemiology and management in China (Table 2). All tests of statistical significance will be carried out at the 0.05 level.

**Table 2 T2:** Additional aspects of HCC management for potential evaluation using data from the HCC BRIDGE China national study.

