## Results

The number of patients enrolled across the various geographic regions captured in the global HCC BRIDGE study is expected to exceed 20,000. For the HCC BRIDGE China national study, a total of 15 sites across China have been selected for inclusion at the time of writing. At present, the anticipated country-wide study population is approximately 9000 patients (Figure 1).

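### Neither the historic-control matching nor the listed model covariates include site, so the country-level sorafenib comparison is open to confounding by hospital

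*Protocol article*

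**What the plan says.** Under Comparator groups, patients treated before sorafenib was available serve as historic controls. They "will be statistically matched within the pool of patient data". The four factors named are age, sex, Child-Pugh status and HCC stage, and the match is to the group given sorafenib from 2008 to 2011. Site, province and region are not matching factors.

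The same section gives calendar years for the two periods (2005 to 2007 and 2008 to 2011) and adds a local rule: "These 2 periods will be differentiated by the first record of sorafenib use at each site".

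Sample size gives each site its own control quota, "100 patients per site between 2005 and 2007 for historic controls", and Results states that "a total of 15 sites across China have been selected for inclusion at the time of writing".

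Data analysis specifies Cox and logistic models. Their listed covariates cover stage, gender, age, disease duration, etiology, liver status, tumor extent, interventions and comorbidities, but not site. It states that "analyses will be conducted at the site and country level" and applies the same plan to sorafenib against other therapies, with treatment added as a covariate. The Discussion names as a limitation that different kinds of center take part and that quality of care may vary between them.

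**The concern.** Whether a patient counts as a control depends on when that patient's own hospital first recorded sorafenib, and each hospital contributes pre-sorafenib patients. The design thus collects same-hospital controls, but the matching as described does not use that link and the listed covariates do not restore it.

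Two things follow for the country-level analysis of overall survival, the primary end point:

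- **Center differences.** If hospitals that use more sorafenib have better or worse survival for other reasons, sorafenib patients are weighted towards those hospitals and their controls are not. The difference between hospitals enters the hazard ratio for sorafenib. A larger sample does not remove it.
- **Calendar time.** If the local rule decides control status, a control from a late-adopting hospital may have been treated in the same years as a sorafenib patient at an early adopter. Matching across hospitals then mixes adoption time with treatment.

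**Working it through.** **The plan's own figure.** The article gives no share of same-site pairs, so there is none to reproduce. The anticipated total of about 9000 does not enter the calculation. It is reached by the 2008 to 2010 quotas alone (15 × 3 × 200 = 9,000); adding the 2011 and historic quotas gives 15 × (600 + 192 + 100) = 13,380. That mismatch is a separate matter. The share below needs equal control quotas, not a particular number of controls.

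**Inputs.** Sites: 15 (Results). Historic controls: 100 per site, the same at every site (Sample size). Matching factors: the four listed under Comparator groups.

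**Share of pairs that cross hospitals.** Let p_i be site i's share of sorafenib patients and q_i its share of historic controls. If matching ignores site and the matching factors are unrelated to site,

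cross-site share = 1 − Σ p_i q_i.

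With equal quotas, q_i = 100 / (15 × 100) = 1/15 for every site. Then Σ p_i q_i = (1/15) Σ p_i = 1/15 = 6.7%, however sorafenib patients are distributed. The cross-site share is 1 − 1/15 = 93.3%, and about 7 of every 100 pairs stay within one hospital. If the quota of 100 is per year, q_i is still 300/4,500 = 1/15.

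**Sensitivity (assumptions, not in the document).**

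| Assumption | Mean cross-site share |
|---|---|
| Both groups share the same unequal site sizes: mild / moderate / strong (Dirichlet 5 / 1 / 0.5) | 92% / 88% / 82% |
| Stage and Child-Pugh mix varies by site: SD 0 / 0.5 / 1 / 1.5 on the log scale | 94% / 92% / 87% / 81% |

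The second row is a simulated 1:1 match without reuse of controls: exact on sex, stage and Child-Pugh class, age within 5 years, with 100 controls and an assumed 40 sorafenib patients per site. These are averages. Single draws go lower: the 5% to 95% range under strong inequality of site size is 72% to 89%. Cross-site pairs are the large majority throughout.

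**What this could do to the hazard ratio.** With no true effect and controls spread equally over sites, the spurious log hazard ratio is approximately

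r × CV × σ,

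where σ is the between-site SD of log hazard, CV the relative spread of sorafenib use across sites, and r the correlation of use with site log hazard. The article gives none of the three. As illustration only, take σ = 0.3 and CV = 0.75:

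- If use is unrelated to site survival, the shift averages zero. Its SD over 15 sites is 0.3 × 0.75 / √15 = 0.058, so the 80% range of the hazard ratio is exp(±1.28 × 0.058) = 0.93 to 1.08.
- If better-outcome hospitals use more sorafenib, with r = −0.77, the hazard ratio is exp(−0.77 × 0.75 × 0.3) = 0.84.
- If worse-outcome hospitals use more, with r = +0.77, it is exp(0.77 × 0.75 × 0.3) = 1.19.

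The result runs from near nothing to a material distortion in either direction, depending on inputs that the document does not contain.

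**The case against.** The other side has good arguments, and several stand.

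- **Contradiction.** A reader might infer that pooled matching contradicts the site-specific period rule. It does not. The rule labels patients as before or after sorafenib; the matching then draws from patients so labelled. The two can coexist, although they are in tension.
- **Site-level analyses.** A reader might infer that these are lost or uncontrolled because few pairs lie within one site. The article never says that they use matched pairs. They adjust for age, gender, stage and liver status among others, and a model fitted within one hospital is free of differences between hospitals. They are a partial check on the bias described here.
- **A site term.** It might be thought useless because it would split the pairs. No paired analysis is specified, and a Cox model stratified by site makes the contrast within site whether or not pairs stay together.
- **Condensed article.** Drawing from the pool may mean no more than drawing from the study's data, and does not expressly exclude a preference for same-site controls in the full protocol. Calipers and matching ratios are normally left to that document. But the article itself lists the matching factors and the covariates, and site is in neither list.
- **Cost of exact matching on site.** With about 100 controls per site, a strict requirement would worsen matches on stage and Child-Pugh status. This stands and shapes the fix.

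**Conclusion.** The point holds for the country-level comparison of sorafenib patients with historic controls: as described, hospital is controlled neither by matching nor by adjustment, in a study that defines its periods by site and acknowledges that care may differ between centers. About 14 in 15 pairs would cross hospitals under equal control quotas and site-blind matching, and roughly 81% to 94% on average under the other assumptions tried. These are calculated shares, not figures from the plan.

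The direction and size of any bias cannot be derived from the document. The hazard ratios under the illustrative inputs show only that it need not be trivial; nothing in the article shows that sorafenib use is related to a site's survival. This is an avoidable weakness in a stated analysis choice that should be corrected. It does not invalidate the study or its site-level analyses.

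**What to change.** For the country-level comparison of sorafenib with historic controls:

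1. Stratify the Cox models by site and include site in the logistic models. Keep the listed covariates, because a pooled match balances the four factors overall but not within each site.
2. In the matching, prefer a control from the same site where an adequate match on the four listed factors exists, then one from the same region, then one from the pool.
3. Report the share of same-site pairs, and keep site-blind pooled matching as a sensitivity analysis.
4. State whether and how site-level analyses use the matched set.

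Site is already recorded, so no new data are needed. The cost is some loss of precision, since a site without both groups adds nothing to a site-stratified contrast, and fewer or coarser matches where sorafenib patients outnumber suitable local controls. The regional step still allows cross-site pairs (15 sites over 7 regions is about two per region), which is why the model should carry site as well.

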**Methods/Design:**

The global HCC BRIDGE study is a multiregional longitudinal cohort trial including patients newly diagnosed with hepatocellular carcinoma between January 1, 2005, and June 30, 2011, who are receiving treatment for hepatocellular carcinoma via sites in the Asia-Pacific, European, and North American regions. The HCC BRIDGE China national study comprises the portion of the global HCC BRIDGE study conducted within mainland China. Patients will be followed from time of diagnosis of hepatocellular carcinoma (post-January 1, 2005) to time of death or December 31, 2011, whichever comes first. Data will be collected on demographic/clinical characteristics, relevant laboratory values, hepatocellular carcinoma/underlying liver disease treatment, tumor response, adverse events, hospitalizations, and overall survival. The primary study end point is overall survival; secondary end points are disease progression, treatment-limiting adverse events, and treatment failure.

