**Outcomes in patient subpopulations**
• Assessment of treatment use and clinical outcomes among patients with:
◦ Traditional HCC risk factors, such as hepatitis B or hepatitis C virus infection (or co-infection), alcoholic liver disease, or cirrhosis
◦ Diabetes or multiple metabolic disorder
◦ HIV co-infection
• Assessment of the impact of underlying disease management on clinical outcomes in these patients
• Evaluation of potential regional/provincial differences in outcomes among patient subpopulations

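### Treatment of the underlying liver disease is collected but is in neither the historic-control matching nor the listed covariates, so a change in it between periods can be credited to sorafenib

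*Protocol article*

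**What the plan says.** **Collected.** The Methods/Design part of the abstract lists "relevant laboratory values, hepatocellular carcinoma/underlying liver disease treatment, tumor response, adverse events, hospitalizations, and overall survival" among the data.

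**Flagged as a possible influence.** Table 2, under outcomes in patient subpopulations, includes "Assessment of the impact of underlying disease management on clinical outcomes in these patients". The patients meant include those with viral hepatitis, alcoholic liver disease or cirrhosis. The table's title gives the status of its items: "Additional aspects of HCC management for potential evaluation using data from the HCC BRIDGE China national study".

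**Matching.** The Comparator groups section sets 2005-2007, before sorafenib, against 2008-2011, with the boundary at each site's first recorded use. Controls from the earlier period are "statistically matched within the pool of patient data by age, sex, Child-Pugh status, and HCC stage".

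**Models.** The Data analysis section states: "Covariates for the models will include disease stage, gender, age, duration of disease, etiology of disease, liver status", and goes on with "tumor size/spread, surgical intervention/number of interventions, and number of comorbidities". The sorafenib comparisons keep this plan and add only a treatment term.

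Treatment of the underlying liver disease is in neither list. Nor is calendar period.

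**The concern.** In the historic comparison every sorafenib patient comes from the later period and every matched control from the earlier one. Any factor that changed between the periods and affects survival is therefore confounded with sorafenib unless it is matched or modelled.

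Treatment of the underlying liver disease is a plausible factor of this kind. The Background names liver cirrhosis and chronic hepatitis B infection as the main risk factors in this population, so many patients could be candidates for such treatment. The primary end point is all-cause mortality, which includes deaths from liver disease as well as from the tumor. More background treatment in the later period would look like a benefit of sorafenib, and less would hide one. A stated aim of the global study is the real-world effect of new treatments such as sorafenib, so this comparison is not a side issue.

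**Working it through.** The plan gives no effect size, power or event target for the sorafenib comparison, so it has no figure of its own to reproduce. The check has two parts.

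**1. The lists side by side**

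| Item | Collected | Matching | Covariates |
|---|---|---|---|
| Age, sex | yes | yes | yes |
| HCC stage | yes | yes | yes |
| Child-Pugh / liver status | yes | Child-Pugh | liver status |
| Etiology | yes | no | yes |
| Underlying liver disease treatment | yes (abstract) | no | no |

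Etiology says which disease is present, and Child-Pugh or liver status says how severe it is. Neither says whether it is being treated. Two patients with the same etiology and Child-Pugh class, one treated and one not, look the same on these variables.

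**2. Size, on assumed inputs**

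The documents give no uptake or effect figures, so all of these are assumptions:
- true sorafenib hazard ratio of 1
- background-treatment mortality hazard ratio h of 0.6 to 0.8
- uptake p0 in 2005-2007 and p1 in 2008-2011
- no other covariates

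For one unadjusted binary confounder:

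apparent HR ≈ [p1·h + (1 − p1)] / [p0·h + (1 − p0)]

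- 20% to 40%, h = 0.6: (0.24 + 0.60) / (0.12 + 0.80) = 0.84 / 0.92 = 0.913
- 20% to 40%, h = 0.8: (0.32 + 0.60) / (0.16 + 0.80) = 0.92 / 0.96 = 0.958
- 20% to 60%, h = 0.6: (0.36 + 0.40) / 0.92 = 0.76 / 0.92 = 0.826
- 20% to 60%, h = 0.8: (0.48 + 0.40) / 0.96 = 0.88 / 0.96 = 0.917
- No change (p0 = p1): exactly 1.00
- Reversed, 40% to 20%: 0.92 / 0.84 = 1.095 for h = 0.6 and 0.96 / 0.92 = 1.043 for h = 0.8

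The formula is approximate because the mix of treated and untreated survivors shifts over follow-up. The large-sample Cox hazard ratio, assuming exponential survival, a 9-month median and 36 months of follow-up, is 0.90 to 0.96 for the first rise and 0.82 to 0.91 for the second. Taking both methods together, the ranges are about 0.90 to 0.96 and 0.82 to 0.92.

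**What this does to a test.** Assume 1000 deaths split 1:1, a two-sided 0.05 level and h = 0.65. The chance of a falsely significant benefit is Φ(|ln HR|·√1000 / 2 − 1.96).
- 20% to 40%: HR = (0.26 + 0.60) / (0.13 + 0.80) = 0.86 / 0.93 = 0.925, chance about 24%
- 20% to 60%: HR = (0.39 + 0.40) / 0.93 = 0.79 / 0.93 = 0.849, chance about 73%

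Without bias it would be 2.5%. More patients do not shrink the bias; they make a false finding more likely.

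**The case against.** The strongest reply is that the mechanism is not in the document. Nothing reports that treatment of the underlying liver disease changed after 2007. The changes that the Background describes are screening and vaccination, and antiviral therapy is not mentioned. A reader might infer from Table 2 that the authors expect this treatment to affect outcome, and from the design that drift in background care is in fact credited to sorafenib. Neither inference is supported. Table 2 lists a potential evaluation, and the bias between periods exists only if uptake moved. This part of the reply stands and limits the point to what can happen.

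Other replies stand in part:
- **Existing adjustment.** Where earlier treatment already shows in liver function, Child-Pugh matching and the liver-status covariate capture some of its effect. The figures above describe crude confounding, so what remains under the plan may be smaller. It is not removed, because treatment itself is not recorded by these variables.
- **Timing of the data.** Only the abstract names this variable. The Data collection section ties collection at diagnosis and at each new intervention to demographic and clinical characteristics, and its treatment items concern HCC. Availability at index treatment, above all in 2005-2007 charts, is not shown.
- **Open list.** The article condenses a fuller plan, and its covariate list is not worded as exhaustive. But the point is not absent detail: two itemised adjustment sets are printed, and both omit a variable that the study collects and flags.
- **Concurrent controls.** A same-period comparison is less exposed to drift. The Comparator groups section, however, uses these controls to evaluate patient characteristics and does not link them to the historic comparison.
- **Limitations.** The Discussion concedes the lack of randomization, but does not mention changes in background care.

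**Conclusion.** The point holds as a gap in the stated adjustment sets, not as a demonstrated bias. A collected variable, whose effect on outcome the authors list for possible study, is left out of both the matching and the covariates of a comparison in which exposure follows calendar time. If its use changed between periods, the change can be credited to sorafenib or can mask an effect.

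Under the stated assumptions the apparent hazard ratio with no true effect is about 0.90 to 0.96 for a 20-point rise in uptake and about 0.82 to 0.92 for a 40-point rise. It is 1.00 if uptake did not change. These ranges rest on assumed uptake, an assumed mortality effect and no other covariates; the documents supply none of these inputs. The gap is worth closing because the remedy is small.

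**What to change.** - Add treatment status for the underlying liver disease, at or before the start of the index treatment, to the covariates in the Data analysis section for the sorafenib comparisons. Do not count later starts: they are known only for patients who survive to them and may be a consequence of the index treatment.
- Add the same variable to the historic-control matching where recording is adequate in both periods.
- Report its prevalence and missingness by period and by treatment group, so that a reader can see whether it changed and whether the two eras recorded it alike.
- Present the historic result beside a same-period comparison with the concurrent controls, adjusted for the same covariates.

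**Cost.** No new patients or procedures. There will be slightly fewer exact matches if the variable is used for matching. The result will depend on chart documentation, which the Discussion already names as a limitation; if recording differs by period, matching on the variable could add bias, which is why covariate adjustment comes first. One covariate does not remove other drift over calendar time, hence the same-period comparison.

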## Methods

### Study design

The global HCC BRIDGE study is a multiregional longitudinal cohort trial including patients diagnosed with HCC from January 1, 2005, to June 30, 2011 [10]. Patients enrolled in the study will be followed from the date of HCC diagnosis to December 31, 2011, or date of death, whichever comes first. The HCC BRIDGE China national study comprises the portion of the global HCC BRIDGE study conducted within mainland China. To ensure that the national study is geographically representative, it was designed to include patients enrolled at sites from all 7 traditional regions across China (North, North-East, East, South, South-West, North-West, and Central).

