### Patients

All patients enrolled in the HCC BRIDGE study must meet 3 key inclusion criteria: (1) diagnosed with HCC between January 1, 2005, and June 30, 2011, in accordance with American Association for the Study of Liver Diseases/European Association for the Study of the Liver guidelines [11]; (2) aged at least 18 years at the time of HCC diagnosis; and (3) received or receiving treatment for HCC through a site enrolled in the HCC BRIDGE trial. Patients participating in other clinical trials will be included in the study if the patient is enrolled in a single-arm clinical trial, enrolled in a randomized clinical trial of HCC adjuvant therapy, or was not selected to receive active treatment in a randomized clinical trial that was conducted between 2005 and 2007. Any patient whose first active HCC-directed treatment is received via participation in a randomized clinical trial of primary HCC therapy will be excluded from the current study, since this treatment regimen would have been determined by a study protocol rather than by the treating physician. Similarly, patients included in the China national study who subsequently enroll in such a trial will be censored from the study at that time point. Patients with unknown month and year of HCC diagnosis or of the first visit at the site of inclusion will be excluded. Furthermore, to preserve regional representation within China, patients who reside outside the province of interest for a particular study site will also be excluded. Finally, in order to avoid selection bias when the number of eligible patients at a site exceeds the number allowed according to study sample size calculations, an enrollment scheme will be adopted such that the same number of consecutive patients are enrolled each month. For example, in the first year of data entry, if a site is to enroll 200 patients, approximately 17 consecutive patients diagnosed with HCC will be enrolled in each month. If there are less than the specified numbers of patients in any given month, we ask that the corresponding number of extra patients be enrolled in the following month.

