**Primary end point**
Overall survival
Number of days from date of treatment initiation to date of death. Death will be verified by sites based on death certificates or via caregiver, relative, or health care provider, and death information source will be captured in data collection. Surviving patients will be censored from last date of treatment assessment.

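### Sorafenib and control groups overlap and the treatment that starts the survival clock is not named, so immortal time or late-line selection could distort the sorafenib survival comparison

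*Protocol article*

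**What the plan says.** Four parts of the article bear on this point.

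- **Groups (Comparator groups).** Sorafenib treatment means use alone, or together with other therapy within a 21-day window; no line of therapy is specified. "Patients treated with non-sorafenib therapies during the period when sorafenib was available will act as concurrent controls"; that sentence goes on to assign them to a comparison of patient characteristics. Historic controls are patients treated before sorafenib was available, "statistically matched within the pool of patient data by age, sex, Child-Pugh status, and HCC stage" to sorafenib patients.
- **Clock (Table 1).** Overall survival is the "Number of days from date of treatment initiation to date of death". Under Study design, patients "will be followed from the date of HCC diagnosis to December 31, 2011, or date of death".
- **Model (Data analysis).** Overall survival is analysed by Cox regression. "The same analysis plan will be adopted for the evaluation of survival and other clinical end points with sorafenib versus other therapies", the one stated change being that treatment is added as a covariate. The model covariates already include duration of disease and number of interventions.
- **Eligibility and data (Patients; Data collection).** Patients qualify if they "received or receiving treatment for HCC through a site enrolled in the HCC BRIDGE trial". The month and year of both diagnosis and first site visit must be known. Characteristics are recorded at every new treatment, so the plan expects several treatments per patient.

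**The concern.** Patients with this disease often have treatments in sequence. Someone given a procedure in 2009 and sorafenib in 2010 meets both the concurrent-control and the sorafenib definition. Someone treated in 2006 who receives sorafenib in 2009 is both a historic control and a sorafenib patient. The article has a censoring rule for patients who enter a randomized trial of primary therapy, but none for a control who starts sorafenib.

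The clock adds to the problem. If it starts at first treatment and patients are classed by whether they ever took sorafenib, users cannot die before they start it. That guaranteed survival is credited to the drug. If it starts at sorafenib for users and at first treatment for everyone else, later-line patients are set against first-line patients. Matching of historic controls uses neither line of therapy nor time since diagnosis.

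At stake is the second of the two aims that the Background gives for the global study: the real-world effect of new treatments such as sorafenib on outcomes. The same data could show benefit or harm depending on a choice the text leaves open.

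**Working it through.** The article gives no HR, event count or power for the sorafenib comparison, so there is no figure to reproduce. The anticipated 9000 patients do not enter the argument.

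**From the article.** Treatment between 2008 and mid-2011 with follow-up to the end of 2011 gives 6 to 48 months of potential follow-up.

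**Assumed.** 6000 patients; median survival 8, 12 or 24 months; 0–10% starting on sorafenib; later starts giving about 9–44% ever-users with a median delay of about 5–9 months. Sorafenib has no effect (true HR 1). In a second setting sorafenib is given at progression, which triples the death hazard.

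**Closed-form check of ever/never use timed from first treatment.** Let λ be the death hazard and s the monthly rate of starting sorafenib, both constant, with no censoring and nobody starting on sorafenib.

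- Never-users: mean survival 1/(λ+s), so death rate λ+s.
- Ever-users: mean survival 1/(λ+s) + 1/λ, so death rate λ(λ+s)/(2λ+s).
- Rate ratio = λ/(2λ+s).

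With a 12-month median, λ = ln 2/12 = 0.0578. For s = 0.01 the ratio is 0.0578/0.1255 = 0.46. For s = 0.03 it is 0.0578/0.1455 = 0.40. Simulated Cox models with censoring gave 0.465 and 0.403, so the mechanism and its size agree.

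**Simulated HRs over all assumed settings, true HR 1.**

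| Reading | Constant hazard | Sorafenib at progression |
|---|---|---|
| First-treatment clock, ever/never sorafenib | 0.38–0.67 | 0.79–0.96 |
| Sorafenib clock for users, first-treatment clock for never-users | 0.69–0.93 | 1.30–2.36 |
| Switchers in both groups, each from its own start | 0.99–1.01 | 1.40–2.50 |
| Sorafenib as a time-dependent covariate | 0.99–1.02 | 1.48–2.53 |
| First treatments only, each from its own start | 0.99–1.03 | 0.98–1.02 |

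The second row falls below 1 at constant hazard because taking later users out of the control group removes patients who lived long enough to switch.

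Double membership by itself did not bias a null effect at constant hazard. With a true HR of 0.7 it diluted the estimate to 0.72–0.76, and the empirical standard error was 0.80–0.89 of the naive one, because rows from one patient are not independent.

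The progression column shows direction more than size. It moves with the assumed rise in hazard and with how many progressing patients receive sorafenib.

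**Historic overlap.** With exponential survival, the share alive three years after a 2006 treatment is 0.5^(36/8) = 4.4%, 0.5^(36/12) = 12.5% or 0.5^(36/24) = 35.4% for medians of 8, 12 and 24 months. Only some of these would start sorafenib.

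**The case against.** The strongest reply is that the article has a time-zero rule, and a benign reading is natural. Table 1 counts several secondary end points by treatment intervention, and characteristics are collected at each new treatment. Taking treatment initiation as the start of the treatment being compared fits that structure and removes classic immortal time for users. This stands in part: the defect is an unnamed index treatment, not a missing rule.

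Several stronger readings are tempting but unsupported:

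- A reader might infer that sorafenib enters the model as a fixed covariate. The article says neither fixed nor time-dependent, and that detail may lie in the full protocol or SAP.
- A reader might take the concurrent-control sentence as defining the survival contrast. It concerns characteristics; the survival contrast comes from Data analysis.
- A reader might call this the study's headline comparison. The aim belongs to the global study, and the China article is framed mainly around treatment patterns, outcomes and unmet need.
- A reader might conclude that overlap alone biases the result, or that the model ignores disease duration and prior treatment. The table above contradicts the first. The listed covariates contradict the second, although when they are measured is not stated, and a count of interventions could include later ones.
- A reader might say that time before the first site visit is counted as at risk. That follows only if the index treatment can predate the visit, which the text leaves open.

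The article's acknowledgement that treatment comparisons are not randomized is fair, but it does not cover a misaligned clock. What survives all this is that the stated groups overlap, the stated clock is ambiguous, and the stated matching omits line of therapy and time since diagnosis.

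**Conclusion.** The concern holds as a defect in stated definitions: group membership is not exclusive and the index treatment is not fixed, so readings that the text permits lead to opposite conclusions. With no true effect, ever/never use from first treatment could give an HR of about 0.38–0.67 at constant hazard, shrinking to 0.79–0.96 if sorafenib follows progression. The mixed clock could give 0.69–0.93 or 1.30–2.36 in the same two settings. These figures depend on assumed survival, uptake, delay and a tripled hazard at progression, none of which the article supplies. They show what could happen, not what will; neither the direction nor the size of any actual bias is established.

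**What to change.** Change the analysis wording as follows.

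1. Define time zero as the start of the treatment line being compared, for sorafenib patients and for both control groups, and assign each line to one group only.
2. Measure stage, Child-Pugh status, duration of disease and number of prior interventions at that time zero. Add line of therapy and time since diagnosis to the matching variables. Starting each line at its own time zero does not by itself remove confounding by progression, as the third row of the table shows.
3. Use standard errors robust to several lines from one patient.
4. State how later sorafenib use in controls is handled, for example by censoring at first use. That censoring may be informative if it coincides with progression, so add a sensitivity analysis.
5. If a time-dependent sorafenib covariate is preferred, pair it with time-updated stage and liver function; used alone it gave 1.48–2.53 under no effect when sorafenib followed progression.
6. Where the index treatment predates the first visit to the study site, use delayed entry at that visit.

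No new data items appear necessary: characteristics are already collected at each new treatment, and the month and year of the first visit are an eligibility requirement. The cost is some lost matches, in a number that cannot be estimated from the article, and modest extra programming.
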